**5.2.3 Data Management**

All data will be collected through the Indian Registry of Intensive Care (IRIS) eCRF platform to ensure data safety and security; for the duration of the study, the site will be a part of the IRIS registry. Each site will have full rights over the data of non-study participants; only anonymised data will be shared with the registry.

**5.2.4 Recruitment and retention**

During the first 4 weeks of the recruitment, the feasibility of the timely completion of the study will be assessed using an internal pilot. Based on the pilot study, the targets will be:

1. Recruit a minimum of 2 tracheostomy and 2 non-tracheostomy patients per week per centre.
2. Participants drop out in the first 4 weeks, <25%.

###### 5.3 Embedded process evaluation and qualitative study (Workstreams 2 & 3)

The process evaluation examined usual care practices, intervention implementation, and maintenance across sites, with specific attention to fidelity, adaptation, and contextual determinants influencing adoption and delivery. During the pre-implementation phase, data focused on characterising usual care, discharge practices, and caregiver preparedness. During implementation and maintenance phases, observations and interviews were used to examine how intervention components were delivered, adapted, or not implemented, and the organisational and professional factors shaping these processes. Barriers and facilitators were explored iteratively using a realist-informed approach and subsequently mapped to the CFIR framework to support interpretation across sites and phases.

**5.3.1 Design and data collection**

A process evaluation will provide an assessment of the intervention's implementation, including how well the implementation follows the protocol (components, timing and duration) and identification of the contextual barriers and facilitators to adoption and implementation. A mixed methods approach will be used whereby quantitative data (as collected from Workstream 1) and qualitative data in the form of field notes, observations, interviews and discussions with the implementation team will be analysed.

**Data sources and types, and timepoints**

**Field notes**

1a. Will be generated during the pre-implementation phase at all sites to examine interpretation, acceptability, and contextual readiness, informed by more than one visit by the central research team and site research personnel;

1b. Three team stakeholder meetings at each site conducted at baseline(pre implementation), at the start of implementation, and during the maintenance phase.

**Observations.**

2. Non-participant observations undertaken by the research team will be taken throughout the study , documenting patient- family- clinician interactions and care processes relevant to the implementation and intervention.

**Semi- structured interviews**

3. Semi-structured interviews with patient–carer dyads conducted approximately one month after recruitment (recruitment is at the time of RFSD), including 3a. Carers who received the intervention and

3b. baseline-period participants describing their lived experience of home discharge without the intervention;

3c. Semi-structured interviews with ICU nursing staff and Site PIs exploring perceptions of usual care, experiences of the intervention, and expectations for future home discharge will be undertaken after completion of the study

**Debriefs**

4. Individual debriefs and group reflective discussions with the project team conducted throughout the study period. (looking at usual care, experiences and expectations).

The study will aim to recruit approximately 12 patient-carers, 6 healthcare workers, and 4 project staff, with sampling targets reviewed iteratively alongside concurrent analysis.

**5.3.2 Recruitment, and consent**

The AIRe study team and researcher undertaking the process evaluation will liaise with the site PI and unit manager to identify suitable observation periods. Before the study begins, the lead researcher will visit each site and explain the process evaluation, allowing staff to ask questions or express concerns.

*a) Observations*

The patient-family of the non-control group being observed will be formally recruited and fully informed about the study. Written consent will be obtained before undertaking observations. For the healthcare workers, formal recruitment will not be practised, but they will be informed about the study, the processes, and their roles. They will be free to deny participating in observations . The researcher will obtain verbal permission to conduct observations on the unit overall. The researcher will ask the ward manager to circulate an email to staff to inform them before observations take place, along with a copy of the participant information sheet. Permissions and refusals will be documented by the researcher, and each observation will last approximately 6-7 hours.

*b) Interviews*

Eligible HCWs/patient-family dyads will be invited by a member of the clinical and/ or the research team to engage in a semi-structured interview. A time and situation conducive to interviews will be identified in every centre, but the site selected may be changed to suit the work pressures and business of the interviewees. Where the interviews are at patient homes (telephonic or physical), at least 24 hrs will be given to suggest a suitable date and time for the meeting. Withdrawal from the study is allowed within the 4 weeks following the interview. The researcher will identify and destroy the data if consent is withdrawn. This will be recorded.

**5.3.3Process evaluation analysis**

Transcripts of all data types (observations, field notes and interviews) will be deductively analysed independently by two researchers ([name]) to identify the key concepts (themes) regarding intervention acceptability, along with barriers and facilitators to implementation. Initially the text will be open-coded by reviewing all text line by line and then descriptive codes will be assigned to the words, sentences and paragraphs in the transcripts. At this stage of the analysis, lines in the transcripts will be linked and grouped as the first set of codes which relate to the current prescribing practices, the experiences of the patient and family dyads, the clinical teams, and research team, along with adaptations to intervention and implementation made. Axial coding in the next step of the data reduction process will link the descriptive codes via repackaging and combine the data to identify categories that have similar characteristics. After developing categories, the relationships between the categories will be explored to reveal higher level themes, and then where relevant to implementation of the intervention mapped to the CFIR framework 2. New themes, and contextual and team factors that emerge from the evaluation but do not fit the existing framework will also be reported.

#

#

# 6.0 PARTICIPANT ELIGIBILITY CRITERIA

###### 6.1 Inclusion Criteria for Controlled Interrupted Time Series (Workstream 1)

1. Adult tracheostomised patients in the neurosurgery ICU, expected to survive beyond and need tracheostomy for more than 2 weeks after being declared 'expected fit to discharge' from the ICU by the treating physician/ surgeon.

2. Age ≥ 18 years

3. Ability and willingness to give written informed consent by Dyads..

###### 6.2 Exclusion Criteria for Controlled Interrupted Time Series (Workstream 1)

1. Patients without an identified family carer willing for home care,

2. Patients needing greater organ support than is manageable at home (home ventilation excluded)

Current participation in an interventional trial with conflicting therapies or primary outcomes

3. Staying beyond a 100 km radius, precluding scheduled home visit

The inclusion and exclusion criteria are broad-based and pragmatic and therefore maximise external validity of the study. The primary outcome is chosen to maximise inclusion of all eligible patients who can safely be cared for at home. Short patient life expectancy post-discharge has not been considered a criterion for exclusion, with the understanding that this will enable informed decision and safe end-of-life care of these patients, often a reality in neuro ICUs. External factors that may influence the primary outcome, such as contextual barriers to the clinician declaring fit-for-discharge or the families' reluctance for home care, have been included to address potential sources of bias arising from them.

###### 6.3 Additional eligibility criteria for process evaluation (Workstream 2)

**6.3.1 Staff participant inclusion criteria**

1. Clinical and non-clinical staff working at the ICU and wards participating in the AIRe study.
2. Age ≥ 18 years
3. Ability to give written informed consent.
4. Ability and willingness to participate in the observations and interviews.

**6.3.2 Staff participant exclusion criteria**

1. Age <18 years
2. Unable to give written informed consent.
3. Unable or unwilling to participate in the observations and interviews.

**6.3.3 Relative/visitor participant inclusion criteria**

1. Relatives accompanying patients (who fulfil workstream one eligibility criteria)
2. Age ≥ 18 years
3. Ability to give written informed consent.
4. Ability and willingness to participate fully in the observations and interviews.

**6.3.4 Relative/visitor participant exclusion criteria**

1. Relatives accompanying patients who do not fulfil the eligibility criteria.
2. Age <18 years
3. Unable or unwilling to participate in the observations and interviews.

###### 6.4 Additional eligibility criteria for qualitative study (Workstream 3)

**6.4.1 Staff participant inclusion criteria**

1. Stakeholders (healthcare workers, project staff, hospital administrative staff) involved in overseeing or recruiting to the AIRe study.
2. Age ≥ 18 years
3. Ability to give informed consent.

**6.4.2 Staff participant exclusion criteria**

1. Age <18 years
2. Unable to give informed consent.

# 7.0 STUDY LOCATION

The study will be located at three tertiary care hospitals in Odisha, India. After home discharge, patient-carer dyads will be followed at home for 30 days over the phone, via a mHealth application and a home visit.

# 8.0 DURATION OF ENROLLMENT AND FOLLOW-UP

The trial will begin pre-intervention data collection for tracheostomised patients for 4 months before implementation of the intervention (over 30 days). After the implementation, data will be collected for 4 months. The individual participant will be enrolled in the ICU and followed up after home discharge for 30 days.

# 9.0 DESCRIPTION OF INTERVENTION AND ADMINISTRATION

The processes of intervention administration will broadly follow those of the pilot intervention.

(Fig. 3 & 4)

###### 9.1 Schedule of Evaluations

|  | ***Screening*** | ***Consent & Rapport Building*** | ***Training D1-D4*** | ***Pre Discharge*** | ***Post Discharge D1-3*** | ***Post Discharge D 6-7*** | ***Post Discharge D28-31*** | ***Follow up*** |
| --- | --- | --- | --- | --- | --- | --- | --- | --- |
| Informed Consent Form | ***X*** |  |  |  |  |  |  |  |
| LIAISE with Treating Team | ***X*** |  |  |  |  |  |  |  |
| Demographics | ***X*** | ***X*** |  |  |  |  |  |  |
| Primary assessment | ***X*** |  |  |  |  |  |  |  |
| Training Assessment |  |  | ***X*** |  |  |  |  |  |
| In hospital/post-discharge  Hai/ new infections  ICU/hospital readmission  Mortality  Adverse events  Cost  QOL, CBS |  | ***X***  ***X***  ***X***  ***X*** | ***X***  ***X***  ***X***  ***X***  ***X*** | ***X***  ***X***  ***X***  ***X***  ***X***  ***X*** | ***X***  ***X*** | ***X***  ***X***  ***X*** | ***X***  ***X***  ***X***  ***X***  ***X***  ***X*** |  |
| Pre-discharge assessment |  |  |  | ***X*** |  |  |  |  |
| mHealth survey |  | ***X*** | ***X*** | ***X*** |  |  | ***X*** |  |
| Day 1-2-3 assessment |  |  |  |  | ***X*** |  |  |  |
| Day 7 assessment |  |  |  |  |  | ***X*** |  |  |
| Day 28 assessment |  |  |  |  |  |  | ***X*** |  |
| General Assessment Form |  |  |  |  |  |  |  | ***X*** |

###### *Table 2: Schedule of evaluations in the intervention group.*

**9.2 Description of Evaluations:** Detailed description in the manual of the intervention and evaluations

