**5.2.2 Secondary outcomes**

i. Patient and Carer Reported Outcomes measured at Day 30.

a. Health-related Quality of Life (QoL) with EuroQOL 3 dimensions (EQ-5D-3L) of patients at hospital discharge and at Day 30 after hospital discharge?

b. Carer Burden Scores (CBS) of carers at hospital discharge and at 30-day post-discharge

c. Alert, Verbal, Pain, Unresponsive (AVPU) scores at discharge and at 30-day

ii. Measures of safety

a. Hospital-acquired infections- central line-associated bloodstream infections, catheter-associated urinary tract infections, ventilator-associated pneumonia, surgical site infections, in the rate of events within groups per unit time.

b. Clinical outcomes – Length of stay in ICU, frequency of bed sores, tracheostomy blockage, Clinical Deterioration (as declared by the treating team in the hospital or deterioration in AVPU status at follow-up), readmission to ICU or hospital (after discharge and up to 30-day follow-up) and mortality at follow-up of 30 days (rate/ unit time).

iii. Measures of process (post-intervention stage)- Implementation Measures

1. Adherence to the intervention

- %Eligible patients approached
- % consented
- % Trained for at least 3 sessions
- Number of sessions missed.
- Subjective and objective scores of carers' confidence post-training
- % using the mHealth app at least once spontaneously after home discharge
- % 1 week home visits completed
- Data entry (completion)

| **Outcome** | **Definition** | **Assumed relationship** |
| --- | --- | --- |
| Time from the clinician's decision of readiness for step down | Time (days) from the Clinician declaring the patient ready for step down to discharge home under a carer or a paid caregiver.  *Home is defined as the usual residence, or family home, or a rental house in the vicinity of the hospital, but not another healthcare facility* | The intervention will reduce hospital length of stay/ bed days. |
| ICU/ HDU length of stay | Time from ICU admission to discharge to an intermediate facility (ie HDU/ ward) within the same hospital | The intervention will reduce ICU length of stay/ bed days. |
| Complications | Hospital-associated infections are defined as clinician-reported suspected/confirmed infection + new fever or new change in antibiotic. | There will be a reduction in HAI following the intervention. |

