| 30 Day Outcomes | Mortality  Quality of Life (EQ5D)  Readmission to the same, or another healthcare facility  Caregiver Burden (by CBS scale) | There will be no worsening in patient and carer outcomes due to the intervention. |

*Table 2. Description of outcomes and assumed relationship with intervention.*

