| Home Visit | Care Quality: Hygiene, equipment use, trache/RT/foley care, calorie tracking, mobilisation  Support: App usage, local HCC contact, medications | ✔ | ✘ | ✘ |
| At Discharge | Dates & Status: Unit/hospital discharge date & time, CPR, discharge note  Trache-Specific: Ongoing trach care, reason for early discharge, diet chart  CG Consistency: Same carer since enrollment, eHealth tools & scores  Outcome Measures: EQ5D, VAS, CBS score, Semi-structured interview | ✔ | ✔ p | ✔ |

Table 3. Data to be collected at different time points. Tpi-Tracheostomy (post-implementation), NT=Non-Tracheostomy, C= pre implementation patients with Tracheostomy) , p=partial

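### Thirty-day follow-up is promised to every participant but no table schedules it for the comparators, so the pre-post comparison of non-fatal 30-day events may rest on unequal detection

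*Combined protocol and SAP*

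**What the plan says.** Three places in the narrative describe follow-up without restricting it to a group. The Scientific Abstract (section 2.0, Methods), directly after the before/after comparison, has every dyad followed until a month after leaving hospital. Section 7.0 says that "patient-carer dyads will be followed at home for 30 days over the phone, via a mHealth application and a home visit". Section 8.0 says: "The individual participant will be enrolled in the ICU and followed up after home discharge for 30 days".

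The safety outcomes depend on that follow-up. Section 5.2.2 lists tracheostomy blockage, bed sores, clinical deterioration (including a fall in AVPU status at follow-up), readmission up to 30 days and 30-day mortality. The outcome table in that section groups mortality, quality of life, readmission and carer burden as 30-day outcomes. It records the assumption "There will be no worsening in patient and carer outcomes due to the intervention", with no comparator and no margin.

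The data-collection tables are narrower. The schedule in section 9.1 has training columns and three post-discharge windows, the last being "Post Discharge D28-31". Its caption is "Schedule of evaluations in the intervention group". The columns of Table 3 (section 10) are defined as "Tpi-Tracheostomy (post-implementation), NT=Non-Tracheostomy, C= pre implementation patients with Tracheostomy". The Home Visit row of Table 3, which ends in "local HCC contact, medications", and its app-distribution row are ticked for T pi and crossed for NT and C. The last ticked row for C and NT is At Discharge (partial for NT). Table 3 has no day-30 row for any group.

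**The concern.** The main risk of the intervention is that tracheostomised patients go home sooner under family care, and the 30-day outcomes are where harm would show. Under section 11 the primary analysis is a pre-post comparison at Sites A and B. Any difference between phases in how events are looked for therefore enters the contrast directly.

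The extra contacts under AIR are part of the intervention, so they cannot simply be given to the baseline phase. If non-fatal events come to light through those contacts and the baseline phase has only one late contact, a safe intervention can look harmful. If some outcome turns out to have no 30-day data at baseline, nothing can be said about worsening on it. Death depends less on the number of contacts, but it still needs a day-30 contact in both phases.

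**Working it through.** **Who is in the intervention group.** Section 1.0 gives about 160 patients in the intervention arm and about 5 discharges per time point. The Scientific Abstract gives 16 time points before and 16 after.

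- 5 × (16 + 16) = 160, which reproduces the stated figure.
- Post-implementation weeks alone give 5 × 16 = 80, which does not.

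So the arm as sized holds about 80 baseline and 80 post-implementation tracheostomy patients. The section 9.1 caption could in principle cover both phases. Against that, the schedule contains Training D1-D4 and an mHealth survey, and Table 3 crosses training and app distribution for C. Read together, the schedule fits AIR recipients.

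**Post-discharge contacts by group, as tabulated.**

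| | T pi | C | NT |
|---|---|---|---|
| D1-3, D6-7, D28-31 (section 9.1) | yes | not shown | not shown |
| Home visit (Table 3) | ✔ | ✘ | ✘ |
| App distribution (Table 3) | ✔ | ✘ | ✘ |
| Day-30 row (Table 3) | none | none | none |
| 30-day follow-up in the narrative | yes | yes, unscheduled | yes, unscheduled |

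The home visit is probably the D6-7 contact, since section 5.2.2 counts one-week visits, so I do not add it as a fourth window. Section 7.0 conflicts with Table 3, because it names the home visit and the app with no group limit.

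Two further details bear on tracing comparators:

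- The Table 3 row with carer contact and address is crossed for C and NT. A contact number appears for them only in the Recruitment row, which is marked partial.
- The one explicit baseline contact at about a month is the qualitative interview (section 5.3.1). It is timed from recruitment, and about 12 patient-carers are planned in total.

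**Illustration of unequal detection.** The documents give no event rates or detection fractions, so all inputs here are assumptions. Let p be the true 30-day risk of a non-fatal event, equal in both phases. Let d1 be the fraction detected under AIR and d0 the fraction detected at baseline. The false excess is p × (d1 − d0).

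With p = 0.20 and d1 = 0.95, the observed AIR risk is 0.20 × 0.95 = 19%.

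| d0 | Observed baseline risk | False excess |
|---|---|---|
| 0.50 | 0.20 × 0.50 = 10% | 9 points |
| 0.60 | 0.20 × 0.60 = 12% | 7 points |
| 0.80 | 0.20 × 0.80 = 16% | 3 points |

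With complete detection under AIR (d1 = 1) and d0 = 0.70, the false excess is 3, 6 and 9 points for p of 10%, 20% and 30%. With d0 = 0.50 it is 5, 10 and 15 points. If d1 = d0, it is zero whatever the risk.

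**The case against.** A reader might infer that 30-day safety is collected only in patients who receive AIR, so that the comparators have no 30-day observations at all. The documents do not support that. The abstract and section 8.0 commit to following every dyad or participant. Table 3 has no day-30 row even for T pi, whose D28-31 assessment is certain from section 9.1, so its silence cannot show that comparators go unfollowed. The arithmetic of 160 also leaves the caption open to a wider meaning. The intervention manual, to which section 9.2 defers the detail, is not among the documents and may hold a comparator schedule.

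Four narrower objections also have force:

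- The Home Visit row mostly records care quality and support. A cross there for patients not given AIR is expected and does not prove that outcomes are missing.
- Blockage, bed sores and deterioration are section 5.2.2 outcomes. They lie outside the 30-day row that carries the no-worsening assumption, and of the events most open to unequal detection only readmission is in both.
- That row states an assumed relationship, not a planned test.
- The likely bias runs against AIR, so it would not create false reassurance.

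All this stands, and it limits the point to unequal and unscheduled ascertainment. It does not remove it. Whatever the manual says, the protocol's narrative and tables disagree, and as tabulated the contacts differ between the phases being compared. A false signal of harm would also be a wrong result.

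**Conclusion.** The point holds as an internal conflict with a consequence for analysis. The 30-day follow-up promised to all is not carried into any schedule for baseline tracheostomy patients or non-tracheostomy controls, and Table 3 gives them fewer post-discharge contacts. Followed as written, the pre-post comparison of readmission, blockage, bed sores and deterioration may show more events under AIR through detection alone.

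The size is unknown. The 9 to 3 points are an illustration resting on an assumed 20% risk, 95% detection under AIR and 50% to 80% at baseline. They should not be read as an estimate for this trial. The documents do not establish that comparator data are absent.

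**What to change.** - Reconcile the Scientific Abstract and sections 7.0 and 8.0 with the section 9.1 schedule and Table 3. Re-caption the schedule to show which columns apply to pre-implementation patients.
- Add a Day 28-31 row to Table 3, full for T pi and C and partial for NT, using one common form: death and readmission with dates, blockage, bed sores, new infection, AVPU, EQ-5D and carer burden.
- Base the pre-post 30-day safety comparison only on that common ascertainment. Report every event found only through the extra AIR contacts in full, but descriptively.
- State the comparator and the analysis behind the no-worsening assumption.
- Section 11 describes baseline collection as completed at Site C and as having preceded re-implementation at Site D, and calls cannot be added for patients already past day 30. For them, state which 30-day data were collected in each phase and limit the comparison to outcomes ascertained the same way in both. Make no statement about worsening for outcomes without comparator data.

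The cost is wording in the tables and the analysis plan, plus one contact per comparator patient that the narrative already promises. The downside is that events known only from the extra AIR contacts leave the comparative table, so they must stay visible in the descriptive report.
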